### Statistical analysis

After completion of the study, all eligible carriers who have been randomised to the treatment arm and received at least 1 dose of eplerenone will be used in the analyses of the primary and secondary efficacy endpoints, as well as in the safety analysis. Safety will be assessed by summarising the incidence and type of adverse events and the changes in laboratory parameters. The proportion of carriers experiencing serious adverse events and the proportion of carriers with noteworthy changes in laboratory parameters will be compared between treatment groups. The analysis of primary endpoints and secondary endpoints will be performed according to their assigned treatment group in accordance with the intention-to-treat principle. Additional analysis sets may be used in exploratory analyses. The number of subjects withdrawing from the study will be tabulated by their reasons for withdrawal and by treatment group. Potenzial biases due to withdrawal of subjects will be investigated. Baseline characteristics will be compared using chi-squared test (or Fisher’s exact test if appropriate). If differences are found, caution will be exercised when interpreting the results of the analyses between groups and methods may be modified to adjust for this difference.

The primary outcome will be presented by Kaplan-Meier curves for the treatment group, followed by the stratified log-rank test using stratification variables. Multivariate analysis will also be used to compare the endpoints between the two groups, adjusting for other variables including sex, age and screening centre. For missing data, the last observations made will be used. Unless stated otherwise, all secondary analyses will be performed using the same subjects included in the primary analysis. Secondary variables will be analysed using an appropriate statistical test, depending on the nature of the variable. Changes in parameters over time in the different treatment groups will be analysed using repeated measurement analysis or techniques that evaluate the timing of endpoints, when appropriate. For all tests, a *p*-value < 0.05 is considered statistically significant. Statistical analysis will be performed in SPSS (IBM SPSS Inc., Chicago, IL, USA; newest version at moment of analysis).

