### Design

This outpatient study is a multicentre, prospective, randomised trial with blinded assessment of endpoints design (PROBE) [20]. The participating centres are the University Medical Center Groningen (which is the coordinating centre and CMR core lab); Amsterdam University Medical Center; Antonius Hospital Sneek and University Medical Center Utrecht. Carriers were randomly assigned to one of the two study arms, either eplerenone or control (no treatment), in a 1:1 ratio. The follow-up period is 3 years (see the section *Study endpoints*).

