## Baseline results

In May 2014, the first participant was included into the study. Because of slow recruitment, in January 2018 it was decided to stop further inclusion of participants and complete the protocolled follow-up duration with the included cohort (*N* = 84). At this point, it had become clear that it was not realistic to assume that enough participants would be included to reach the originally defined composite primary endpoint (Tab. 3). Instead of a composite dichotomous endpoint, i.e. using the pre-specified cut-off values, individual components of the primary endpoint will now be analysed on a continuous scale to investigate possible significant differences. The statistical analysis plan was amended accordingly, and the decision to amend the study design, i.e. to stop inclusion of participants and to continue with the included cohort, was supported by the DSMB and the medical ethics committee. The primary objective remains showing that eplerenone retards disease progression. The majority of participants have now finished the study and the remaining participants are expected to finish in 2021.

An overview of the baseline characteristics of the 84 participants is provided in Tab. 4. By design, at baseline, all participants were in NHYA class I and had an LVEF > 45% and less than 2500 ventricular premature complexes (VPCs) during 24-hour Holter monitoring. Mean LVEF was 60% (±0.04). The median number of VPCs was 8 (0-1861). Baseline CMR scans were obtained for all 84 participants, but image quality was insufficient to perform adequate analyses in six cases. In the remaining 78 cases, as many as 14 cases (18%) showed LGE, mainly in the inferolateral left ventricular wall, suggestive of myocardial fibrosis. The six cases with insufficient image quality will be included for analysis of the other endpoints. An illustrative example is shown in Fig. 2. There were no statistically significant differences between the two groups in any of the baseline characteristics.

**Table 4 Tab4:** Baseline characteristics: no statistical differences between eplerenone and control group

	All	Eplerenone group	Control group
Number, *n*	84	42	42
Age at inclusion, years (SD)	39.5 (±13.1)	40.2 (±13.0)	38.8 (±13.4)
Male sex, *n* (%)	37 (44)	18 (43)	19 (45)
Body mass index, kg/m^2^ (SD)	25.7 (±4.8)	26.5 (±5.6)	24.9 (±3.6)
Systolic blood pressure, mm Hg (SD)	124 (±16)	128 (±17)	121 (±13)
Diastolic blood pressure, mm Hg (SD)	74 (±11)	75 (±10)	74 (±11)

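### The stated analysis set carries an at-least-one-dose condition that only the eplerenone arm can fail, which contradicts the intention-to-treat claim in the same paragraph

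*Protocol article*

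**What the plan says.** All of the wording at issue is in one section of the protocol article, Statistical analysis.

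- The population is given as "all eligible carriers who have been randomised to the treatment arm and received at least 1 dose of eplerenone". These carriers "will be used in the analyses of the primary and secondary efficacy endpoints, as well as in the safety analysis". No sentence says which controls enter.
- A few sentences later, the primary and secondary endpoints are to be analysed "according to their assigned treatment group in accordance with the intention-to-treat principle".
- The set carries forward: unless the plan says otherwise, "all secondary analyses will be performed using the same subjects included in the primary analysis".
- Two-group comparisons are planned. Serious adverse events and laboratory changes are compared between groups, a stratified log-rank test is specified, and "Multivariate analysis will also be used to compare the endpoints between the two groups".

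Three other places matter. The Design section defines control as no treatment, and the abstract calls the trial open-label. The Treatment section says that eplerenone was begun on the day of randomisation. Baseline results gives 84 participants, 42 per group.

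**The concern.** The two population statements cannot both be followed. Under intention-to-treat, a carrier randomised to eplerenone who never took a tablet is analysed in the eplerenone group. Under the at-least-one-dose condition, that carrier is left out. Analysing the remaining carriers by assigned group does not bring back the one removed.

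A first-dose condition is usually defended on the ground that both arms face it. In a placebo-controlled trial, a participant who never starts is lost from either arm by the same process, without knowledge of the allocation. Neither part of that defence applies here. Controls have no first dose to miss, and participants know their allocation. A carrier who declines eplerenone on learning the allocation would be dropped, while the comparable person in the control group stays. The groups compared are then no longer those formed by randomisation.

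What is at stake is the definition of the primary population. If the wording stands, either of two sets could be defended from the text after the data are seen.

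**Working it through.** **Setting the statements side by side**

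| Participant | At-least-one-dose sentence | Intention-to-treat sentence |
|---|---|---|
| Eplerenone, at least one dose | in | in |
| Eplerenone, never dosed | out | in |
| Control | not mentioned | in |

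The second row is a direct conflict. The third is a gap that the planned between-group comparisons fill by implication.

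**Is there a plan figure to reproduce?** None concerns the analysis set. The sample size is not in dispute: 64 per group for 50% against 25% reproduces with a two-sided Fisher exact test (exact power 80.2% at 64 per group, 79.4% at 63).

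**How much one exclusion weighs.** Each never-dosed carrier removed is 1/42 = 2.4% of the eplerenone arm. Baseline results says that the components are now analysed on a continuous scale. If k of 42 are removed, with mean change *mx* among those removed and *mk* among those kept, the arm mean over all 42 is (k·*mx* + (42 − k)·*mk*)/42. Dropping the k therefore shifts the arm mean by (k/42)(*mk* − *mx*). One exclusion moves it by 2.4% of the difference between kept and removed; two move it by 2/42 = 4.8%.

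**Assumed worst case on the superseded binary endpoint.** The article gives no count of never-dosed carriers, so k is an assumption. Further assumptions: no true effect, 50% progression in both arms (the design's control rate), and every removed carrier a progressor. The apparent eplerenone rate is (21 − k)/(42 − k). With d = 0.5 minus that rate, pooled p = (42 − k)/(84 − k) and SE = √[p(1 − p)(1/42 + 1/(42 − k))], the approximate two-sided rejection rate is Φ(d/SE − 1.96) + Φ(−d/SE − 1.96).

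| k (assumed) | Apparent eplerenone rate | Rejection rate, nominal 5.0% |
|---|---|---|
| 1 | 20/41 = 48.8% | 5.1% |
| 2 | 19/40 = 47.5% | 5.6% |
| 4 | 17/38 = 44.7% | 7.6% |
| 6 | 15/36 = 41.7% | 11.4% |

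For k = 4: p = 38/80 = 0.475, SE = 0.112, d = 0.053, d/SE = 0.47, which gives 7.6%.

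**If exclusions are unrelated to outcome**, only power is lost. With 42 per arm and 50% against 25% (normal approximation), power falls from 66.3% to 65.7% for k = 1 and to 62.4% for k = 6.

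**The case against.** The best defence is that the paragraph is loosely worded and the intention is clear. Much of that stands.

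- **Controls.** A reader might infer that the control arm, half the cohort, is excluded from every analysis. The text does not support that as a plan. The sentence does not say "only", and the same section compares the two groups repeatedly.
- **Unreadable scans.** A reader might also infer that "eligible" lets the sponsor remove the participants whose baseline "image quality was insufficient to perform adequate analyses in six cases", since LVEF by CMR is an entry criterion. Baseline results points the other way: it keeps those six for the remaining endpoints and states that every participant had an LVEF above 45%.
- **Non-starters.** None is reported, and starting on the day of randomisation leaves little room for them. The table above is an assumed worst case, not an estimate, and even so one or two exclusions barely move the error rate.
- **Secondary analyses.** The carry-over of the set is a default that the plan may override. Additional sets are allowed for exploratory work, and bias from withdrawal is to be investigated.
- **Convention.** At least one dose is a normal condition for the treated arm of a safety set. The trouble is that one sentence serves both safety and efficacy.
- **The full plan.** The amended statistical analysis plan is not shown and may word the set correctly.

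None of this removes the conflict over a never-dosed eplerenone carrier. An article may leave analysis sets to the full plan, but this one states a set and then contradicts it.

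**Conclusion.** The concern holds as a contradiction in the stated primary population. The at-least-one-dose condition can exclude randomised carriers from the eplerenone arm only, and that is incompatible with the intention-to-treat statement beside it. The absence of a rule for controls is most likely a drafting slip.

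The practical effect is probably small. Each exclusion is 2.4% of an arm of 42, and it biases the result only so far as those removed differ in outcome from those kept. That judgement rests on there being few or no never-dosed carriers, which the start date suggests but the article does not state. If all 42 took at least one dose, the condition removes nobody and the correction changes no result. The documents do not support a claim that controls, or the six participants with unreadable scans, are to be excluded, or that a material bias has occurred.

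**What to change.** Replace the population sentence in the Statistical analysis section, and the matching wording in the amended statistical analysis plan if it is repeated there, along these lines:

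- *Efficacy set:* all 84 randomised carriers in both arms, in the group assigned, regardless of whether any dose was taken. The six participants without analysable baseline CMR remain in the set for the other endpoints, as Baseline results already says.
- *Safety set:* all eplerenone participants with at least one dose, plus all randomised controls.
- *Sensitivity analysis only:* any efficacy analysis restricted to eplerenone participants with at least one dose.

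The report should also give the number of eplerenone carriers never dosed, even if it is zero, because that number settles whether the point mattered.

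The cost is a few sentences. No new data, visits or participants are needed. The plan has already been amended once for the change of endpoint, so a further correction is feasible, and it should be made before the outcome data are analysed.

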### Study endpoints

The primary and secondary endpoints are listed in Tab. 3. The primary endpoint is a multiparametric assessment of disease progression defined as a responder-based composite primary endpoint (Tab. 3). If one of the predefined parameters of the composite primary endpoint is reached, CMR imaging is performed and study end date recorded. After a follow-up period of 3 years, outcomes will be assessed by an independent adjudication committee blinded to the allocated group. In case of a favourable trend (but no significant effect as yet), the DSMB may advise continuing the study for 2 more years (“adaptive design”).

**Table 3 Tab3:** Primary and secondary endpoints

*Primary endpoint*^a^
LV end-diastolic volume, increase > 10% (assessed with CMR)
LV ejection fraction, absolute decrease > 5% (assessed with CMR)
RV end-diastolic volume, increase > 10% (assessed with CMR)
RV ejection fraction, absolute decrease > 5% (assessed with CMR)
Late enhancement, absolute increase > 5% (assessed with CMR)
QRS voltage, decrease > 25% (ECG, measured in I, II and III in mV)
Occurrence of non-sustained ventricular tachycardia (Holter monitoring, exercise testing)
Heart failure signs and/or symptoms or arrhythmias necessitating medical treatment according to the guidelines and likely due to arrhythmogenic cardiomyopathy
*Secondary endpoints*
All individual components of the primary endpoint
Diagnosis of DCM (according to Mestroni criteria [19])
Diagnosis of ARVC (according to revised task force criteria [18])
Development of global or regional dysfunction and structural alterations (according to revised task force criterion 1 [18])
QRS axis (12-lead ECG)
Conduction intervals (PR interval, QRS duration [12-lead ECG; SA-ECG])
STT segment changes (12-lead ECG)
Change in biomarkers
Occurrence of sustained ventricular tachycardia or ventricular fibrillation
Hospitalisation for a cardiovascular reason

*LV* left ventricular, *CMR* cardiac magnetic resonance*, RV* right ventricular,* ECG* electrocardiogram,* DCM* dilated cardiomyopathy, *ARVC* arrhythmogenic right ventricular cardiomyopathy,* SA-ECG* signal-averaged electrocardiography

^a^The primary endpoint is a multiparametric assessment of disease progression defined as a responder-based composite primary endpoint. If one of the predefined parameters of the composite primary endpoint is reached, CMR imaging is performed and study end date recorded

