### Sample size estimation

This clinical trial was designed based on the assumptions that 50% of the presymptomatic PLN p.Arg14del carrier group without treatment will reach the primary endpoint within 3 years and that treatment with eplerenone is expected to reduce this percentage by 50%. To ensure at least 80% power to detect a difference between the control group and the eplerenone group, at a significance level of 0.05, 128 carriers (64 in each group) are needed. To account for 10–15% loss to follow-up during the study, we aimed to include 150 subjects.

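### Serious adverse events are compared as crude proportions although a participant's study can end at the first efficacy event; if safety collection ends there too, observation time differs by arm, with a small effect

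*Protocol article*

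**What the plan says.** All places are in the protocol article.

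- **Statistical analysis.** The safety comparison between treatment groups uses "The proportion of carriers experiencing serious adverse events", together with the proportion with notable laboratory changes. No person-time or time-to-event measure is named for safety. For the primary outcome the same section uses Kaplan-Meier curves and a stratified log-rank test, which do allow for unequal follow-up.
- **Study endpoints and the footnote to Table 3.** When any one component of the composite is met, "CMR imaging is performed and study end date recorded".
- **Treatment and Table 2.** Eplerenone continues to the end of the study. ECG, Holter and exercise testing are yearly. CMR is scheduled at baseline and month 36 only.
- **Sample size estimation.** The design assumes that "50% of the presymptomatic PLN p.Arg14del carrier group without treatment will reach the primary endpoint within 3 years" and that eplerenone halves this.
- **Baseline results.** Inclusion stopped in January 2018 at 84 carriers, 42 per arm. The dichotomous composite was replaced by its components on a continuous scale, and the cohort is to complete its planned follow-up. Nothing is said about whether the early end date was kept.

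**The concern.** Two crude proportions are comparable when both arms are watched for the same time. Here an individual's study can close at an efficacy event, and the plan expects that event twice as often in controls as on eplerenone. If SAE collection closes with it, randomisation does not balance observation time, because that time is itself an outcome of treatment.

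With equal SAE rates in the two arms, the arm that progresses less is watched longer and accumulates a higher crude proportion. If eplerenone instead worsened disease, its users would leave earlier and harm would be diluted. Few SAEs are to be expected in 84 presymptomatic carriers, so a shift of one carrier can change how a small table reads.

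**Working it through.** **Inputs from the article.** Three-year endpoint proportions of 0.50 (control) and 0.25 (eplerenone), and the planned 64 per group (Sample size estimation); 1:1 allocation and 3 years of follow-up (Design); visit schedule (Treatment, Table 2); 42 per arm (Baseline results).

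**Assumptions.** The article gives no SAE rate. I take equal constant rates *r* of 0.02, 0.05 and 0.10 per year in both arms, and suppose that SAE collection ends at the recorded end date. Let *f* be the share of the three-year endpoint risk that can be detected before month 36, taken as equal in both arms.

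**The plan's own figure.** For 0.50 versus 0.25, a two-sided Fisher exact test at 0.05 has power 0.802 with 64 per arm and 0.794 with 63, so 64 per group (128 in total) is reproduced. Allowing for loss, 128/0.90 = 142.2 and 128/0.85 = 150.6, in line with the target of 150. The 50% versus 25% assumption is therefore the right basis for what follows.

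**Mean observation time if every endpoint can end follow-up early (*f* = 1).**

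- Continuous detection: hazard λ = −ln(1 − *p*)/3, and mean time = *p*/λ. Control: λ = 0.2310, 0.50/0.2310 = 2.16 years. Eplerenone: λ = 0.0959, 0.25/0.0959 = 2.61 years. Ratio about 1.20.
- Detection at yearly visits: mean time = 1 + S + S², with S = (1 − *p*)^(1/3). Control: 1 + 0.794 + 0.630 = 2.42. Eplerenone: 1 + 0.909 + 0.825 = 2.73. Ratio 1.13.

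**Why these are upper bounds.** Five of the eight components in Table 3 are CMR measures, scheduled after baseline only at month 36, when follow-up ends anyway. Early ends can be set off only by QRS voltage, non-sustained ventricular tachycardia, or heart failure or arrhythmia needing treatment. Replacing *p* by *f* × *p* in the same formulas gives:

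| *f* | Detection | Control (years) | Eplerenone (years) | Ratio |
|---|---|---|---|---|
| 1 | continuous | 2.164 | 2.607 | 1.205 |
| 1 | yearly | 2.424 | 2.734 | 1.128 |
| 0.5 | continuous | 2.607 | 2.808 | 1.077 |
| 0.5 | yearly | 2.734 | 2.871 | 1.050 |
| 0.25 | continuous | 2.808 | 2.905 | 1.035 |
| 0.25 | yearly | 2.871 | 2.937 | 1.023 |

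**Crude SAE proportions with no true difference in rate.** Continuous: *r*/(*r* + λ) × [1 − exp(−3(*r* + λ))]. Yearly: (1 − e)(1 + eS + e²S²), with e = exp(−*r*). The excess is 42 × the difference between arms.

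| *f* | Detection | Proportions at *r* = 0.05 (control vs eplerenone) | Ratio | Excess carriers in 42 at *r* = 0.02 / 0.05 / 0.10 |
|---|---|---|---|---|
| 1 | continuous | 10.1% vs 12.2% | 1.20 | 0.36 / 0.85 / 1.54 |
| 1 | yearly | 11.3% vs 12.7% | 1.12 | 0.25 / 0.59 / 1.06 |
| 0.5 | continuous | 12.2% vs 13.1% | 1.08 | 0.16 / 0.38 / 0.70 |
| 0.5 | yearly | 12.7% vs 13.4% | 1.05 | 0.11 / 0.26 / 0.47 |
| 0.25 | continuous | 13.1% vs 13.5% | 1.03 | 0.08 / 0.18 / 0.33 |
| 0.25 | yearly | 13.4% vs 13.6% | 1.02 | 0.05 / 0.12 / 0.22 |

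In every row the true SAE rate ratio is 1.00 by construction, and a comparison per person-year would recover it.

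**The case against.** **The premise is an inference.** A reader might conclude that safety observation stops at the first efficacy endpoint. The article does not say so. It records an end date and is silent on adverse-event collection afterwards. The reporting window is also something a condensed article properly leaves to the full protocol, so its absence is no fault. This stands, and the point is therefore conditional. What the article does state is the measure: a crude proportion, next to a rule under which individual follow-up can differ by arm.

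**The direction is not settled.** A reader might infer that an effective drug would necessarily look less safe. That needs equal SAE rates in both arms. Sustained ventricular arrhythmia and cardiovascular hospitalisation are themselves secondary endpoints, and an effective drug could reduce such events, which works the other way. Only the exposure effect has a known sign.

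**The rule may have lapsed.** After January 2018 the composite is no longer analysed as an event. If the early end date went with it, carriers still in follow-up then would not leave early. The article does not report that it was withdrawn and still states it in the present tense. Inclusion began in May 2014, so some carriers were followed before the change.

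**Bias in the reports to the data and safety monitoring board.** This too might be inferred, but Study organisation and monitoring does not say how those reports express SAEs, so the documents do not support it.

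**Size.** A shift of this order would be hard to detect with 42 per arm. That is true and limits the weight of the point. It does not make the crude proportion the better measure.

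**Conclusion.** The point holds as a small, conditional weakness in the stated safety comparison. If SAE collection ends at the recorded end date, observation time depends on the treatment effect. On the design assumptions it is at most about 13% to 20% longer on eplerenone, and more plausibly about 2% to 8%. The upper-bound excess is about 0.4 to 1.5 carriers in 42, and at most 0.7 if half the endpoint risk can be detected before month 36.

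These figures rest on the plan's 50% versus 25%, constant hazards, the same detectable share in both arms, and assumed equal SAE rates of 2% to 10% per year. The net bias in the real comparison could have either sign. The change is worth making because it is a better measure at little cost, not because the expected distortion is large.

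**What to change.** In the Statistical analysis section:

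1. Report person-years of safety observation by arm.
2. Beside the crude proportions, compare SAEs by time to first SAE, censored at the last safety contact, or as events per person-year.
3. Show separately those SAEs that are themselves efficacy events.
4. State whether SAEs are collected to 3 years regardless of endpoint, and whether the early end date still applied after January 2018.

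The cost is a little more analysis work, using dates that the trial already records. A rate per person-year assumes a roughly constant SAE rate; time to first SAE avoids that. Both correct for the length of observation, but not for any link between progression and later SAE risk, which is why item 4 matters. If collection did stop at the endpoint, filling the gap now would be largely retrospective, because most participants have finished. In that case the statement and the exposure-adjusted comparison are the practical minimum. No efficacy analysis changes.

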**Baseline results:**

A total of 84 presymptomatic PLN p.Arg14del carriers (*n* = 42 per group) were included. By design, at baseline, all participants were in New York Heart Association (NHYA) class I and had a left ventricular ejection fraction > 45% and < 2500 ventricular premature contractions during 24-hour Holter monitoring. There were no statistically significant differences between the two groups in any of the baseline characteristics. The study is currently well underway, with the last participants expected to finish in 2021.

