### Treatment

In the treatment arm, eplerenone was initiated on the day of randomisation at 50 mg orally once daily. The dose of 50 mg once daily is the recommended dose in patients with heart failure. Carriers are maintained at this target dose, or the maximum tolerated dose, until the end of the study. Serum potassium and estimated glomerular filtration rate (eGRF) are monitored at the start of the study, 1–2 week(s) after study start and yearly, and these measures are documented together with the other investigations and vital parameters. The dose is reduced if needed, i.e. in case of hyperkalaemia (serum potassium > 5.5 mmol/l). Carriers undergo yearly follow-up in the cardiology outpatient clinic at each participating centre following routine clinical care. Physical examination, blood sampling (when treated with eplerenone), electrocardiogram, Holter monitoring and ergometry are performed every 12 months. CMR imaging and SA-ECG are performed at the start and end (36 months) of the study (Tab. 2).

**Table 2 Tab2:** Overview of study procedures

	Visit 1 start	Visit 2 1 week	Visit 3 1 year	Visit 4 2 years	Visit 5 3 years
Visit to outpatient clinic	*✔*	**–**	*✔*	*✔*	*✔*
History and current status	*✔*	**–**	*✔*	*✔*	*✔*
Physical examination	*✔*	**–**	*✔*	*✔*	*✔*
Electrocardiogram	*✔*	–	*✔*	*✔*	*✔*
Echocardiogram	*✔*	–	*✔*	*✔*	*✔*
Holter monitoring	*✔*	–	*✔*	*✔*	*✔*
Ergometry	*✔*	–	*✔*	*✔*	*✔*
Signal-averaged ECG	*✔*	–	–	–	*✔*
CMR	*✔*	–	–	–	*✔*
Blood analysis	*✔*	*✔*^a^	*✔*^a^	*✔*^a^	*✔*

Note: Subjects undergo several investigations as summarised in this table. They are requested to visit the outpatient clinic at baseline and at 1‑year intervals thereafter. Subjects randomised to eplerenone visit the outpatient clinic or their general practitioner after 1 week to check serum potassium and eGRF, which are also checked in these subjects at the yearly visits. Of note, all investigations except blood analysis are already performed as part of routine clinical care, which routinely includes evaluation of signs and symptoms of DCM and ACM. For the purpose of the study, we collect and use these available data.

*ECG* electrocardiography, *CMR* cardiac magnetic resonance, *eGFR* estimated glomerular filtration rate, *DCM* dilated cardiomyopathy, *ACM* arrhythmogenic cardiomyopathy

^a^ only for subjects randomised to eplerenone

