### Biomarkers

Venous blood samples from all participants are stored and analysed for levels of biomarkers of fibrosis [21] and for biomarkers of apoptosis, haemodynamic status and inflammation. We will investigate whether these biomarkers predict disease progression. In addition to the volume of blood needed to measure these biomarkers, additional blood (serum and plasma) is taken and stored to allow for additional analyses in the future (samples stored for a maximum of 15 years). The amount of blood taken per venipuncture is 20 ml (at the start of the study and after 3 years). Carriers were asked to give their written informed consent for these additional analyses at the start of the study.

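### The planned between-arm comparison of laboratory changes rests on four scheduled follow-up blood analyses on eplerenone and at most one in control; if any follow-up value counts, it is biased against eplerenone

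*Protocol article*

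**What the plan says.** The safety part of the Statistical analysis section of the protocol article plans a test per carrier between arms: "the proportion of carriers with noteworthy changes in laboratory parameters will be compared between treatment groups". It defines neither noteworthy nor the visits that count.

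The sampling schedule is in the Treatment section. In Table 2 the blood analysis ticks at 1 week, 1 year and 2 years carry a footnote, "only for subjects randomised to eplerenone"; the ticks at the start and at 3 years do not. The body text ties the 12-monthly draw to treatment in the same way: "blood sampling (when treated with eplerenone". The table note adds: "Subjects randomised to eplerenone visit the outpatient clinic or their general practitioner after 1 week to check serum potassium and eGRF", and then, of potassium and eGFR, "which are also checked in these subjects at the yearly visits".

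The Biomarkers section gives the sampling that applies to all participants: "at the start of the study and after 3 years".

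**The concern.** The chance that a person shows at least one abnormal value grows with the number of times that person is tested. A proportion of carriers with a noteworthy change, compared between one arm tested four times and another tested at most once, therefore measures testing intensity as well as the drug.

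The Discussion names hyperkalaemia as the most important side-effect of eplerenone, so this is the laboratory safety result that readers will look for. If the comparison is run on any follow-up value, an excess on eplerenone could not be divided into a part due to the drug and a part due to extra testing. A real excess could then be dismissed as an artefact, and an artefact reported as harm.

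**Working it through.** **Scheduled follow-up draws per carrier (Table 2).** Eplerenone: 1 week, 1 year, 2 years, 3 years = 4. Control: 3 years = 1. One is the most that control can have. The common 3-year draw is explained under Biomarkers, while the table note describes yearly potassium and eGFR checks for the eplerenone arm. If the control sample at 3 years was used for biomarkers only, the safety count is 4 against 0. Routine care is not said to fill the gap, since "all investigations except blood analysis are already performed as part of routine clinical care".

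**Arm size.** "A total of 84 presymptomatic PLN p.Arg14del carriers" were included, 42 per arm.

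**Assumptions.** The article gives no rate of noteworthy values. I take the same per-draw probability p in both arms (no drug effect), with p = 1%, 2%, 5% and 10% as an assumed range. A carrier counts if any follow-up value is noteworthy. Tests are two-sided at 0.05; the article gives 0.05 but not the sidedness.

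**Independent draws.** The proportion counted after k draws is 1 − (1 − p)^k, with k = 4 for eplerenone and k = 1 for control. For p = 5%: 1 − 0.95^4 = 18.5% against 5%, ratio 3.71. The last two columns give the probability of a significant result with no drug effect, enumerated over both binomial distributions at 42 per arm.

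| p per draw | Eplerenone | Control | Ratio | Expected carriers of 42 | Fisher | Chi-squared |
|---|---|---|---|---|---|---|
| 1% | 3.9% | 1% | 3.94 | 1.7 vs 0.4 | 0.4% | 5.6% |
| 2% | 7.8% | 2% | 3.88 | 3.3 vs 0.8 | 5.0% | 21.8% |
| 5% | 18.5% | 5% | 3.71 | 7.8 vs 2.1 | 37.0% | 53.1% |
| 10% | 34.4% | 10% | 3.44 | 14.4 vs 4.2 | 72.6% | 80.0% |

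**Correlated draws.** Repeated values in one person are not independent, so the table above is an upper bound. In a latent-normal model, draw j is noteworthy when √ρ·b + √(1 − ρ)·e_j exceeds the normal quantile for 1 − p. Here b is shared within the carrier, e_j is specific to the draw, and ρ is the within-carrier correlation. Simulating 1,000,000 carriers at p = 5% (control 5%) gives:

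| ρ | Eplerenone | Ratio | Fisher | Chi-squared |
|---|---|---|---|---|
| 0.3 | 16.4% | 3.27 | 26.3% | 42.8% |
| 0.5 | 14.5% | 2.89 | 18.0% | 33.9% |
| 0.7 | 12.0% | 2.41 | 9.7% | 23.1% |
| 0.9 | 8.8% | 1.75 | 2.9% | 11.2% |

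At ρ = 0.9 the ratio is 1.91 for p = 2% and 1.63 for p = 10%. The excess shrinks but does not vanish.

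**One common draw.** With one follow-up draw in each arm, the two proportions are equal when the drug has no effect. Over p = 1% to 10% the false-positive probability is at most 1.8% (Fisher) or 0.1% to 5.9% (chi-squared).

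**The case against.** The strongest objection is that the any-visit rule is inferred. The article does not say that a value at any visit counts, and it does not exclude a comparison of baseline with 3 years, for which Table 2 has unmarked ticks in both arms. Counting rules are commonly left to the analysis plan, and the Baseline results section confirms that one exists and was amended. If that plan uses only the 3-year visit, the bias disappears. This stands, and it makes the point conditional. It does not dispose of it: the article itself fixes both the per-carrier comparison and the unequal schedule, and nothing in it restricts the comparison to common visits.

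Three stronger readings go further than the documents allow.

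- A reader might infer that the comparison is bound to show a significant excess. It is not. At rates of 1% to 2% with 42 per arm, a significant result is unlikely even with independent draws, although the estimate stays inflated. The Discussion describes these participants as having normal renal function and very low risk, which makes the higher rates less plausible for a strict potassium threshold.
- A reader might take 3.4 to 3.9 as the expected ratio. It is the extreme case, with no within-carrier correlation.
- A reader might infer that the last-observation rule for missing data adds control baselines as unchanged values. That rule stands with the primary and secondary outcomes and is not tied to safety data, and draws that were never scheduled are not missing data.

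It is also fair to say that this is a supporting safety summary, that Table 2 shows the schedule openly, and that the bias runs against the drug and so does not conceal harm. That limits the importance of the point but does not make the comparison interpretable.

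**Conclusion.** The concern holds in conditional form. Four scheduled follow-up blood analyses against at most one is a plain count from Table 2. On the natural reading, that a carrier counts if any follow-up value is noteworthy, the stated comparison is biased against eplerenone with no drug effect present. The direction is certain on that reading; the size is not, because it rests on assumed per-draw rates and correlations. The no-effect ratio is at most 3.4 to 3.9 for rates of 2% to 10%, and about 1.75 to 2.4 at a rate of 5% with correlation 0.9 to 0.7. Whether this would reach significance with 42 per arm depends on the rate. An analysis plan that already limits the test to 3 years would remove the problem.

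**What to change.** Before any analysis, confirm that potassium and eGFR were measured in controls at 36 months.

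- If they were, state that any between-group laboratory test uses only the visit sampled in both arms: change from baseline to 36 months, adjusted for baseline. Tabulate the week-1, year-1 and year-2 values for eplerenone descriptively, with no test.
- If they were not, drop the between-group laboratory test and report the eplerenone values descriptively only.

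The change takes a sentence or two in the analysis plan and needs no new data; with most participants already finished, added control sampling could not supply the earlier visits. The cost is in what can be concluded. Early or transient changes will have no control figure. The 36-month eplerenone values also come after any dose reduction for hyperkalaemia described under Treatment, so they may understate the drug effect. Both limits should be stated beside the result.
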